### Randomization and blinding

The stratified block randomization method will be used by a researcher who is not involved in the trial. Randomization will be stratified by the surgery site (stomach or intestine) and age (<60 years or ≥60 years) and is planned to be conducted by using IBM SPSS Statistics version 25.0 software (IBM SPSS, Armonk, NY, USA). It will be performed to generate a random number table that will allocate the eligible participants to either of the two groups (the EA group or the control group) in a 1:1 ratio after the participants have signed printed informed consent forms. The random allocation cards will be made and sealed in opaque envelopes. Participants will be assigned to different groups by the Clinical Research Coordinator who will also be responsible for informing the acupuncturists regarding the group allocation. Blinding of the acupuncturists is difficult to conduct due to the characteristics of acupuncture; thus, participants and other researchers except acupuncturists will be blind to the treatment allocation including the outcome assessors and data statisticians. Participants will be arranged to different ward rooms for avoiding communicating with other participants. At the end of the last treatment, all participants will be asked to answer which group they’re allocated aiming at evaluating the success rate of blinding.

### Interventions

After signing the informed consent forms, all the eligible participants will be randomized into one of the two groups (the EA group or the control group). Participants of the EA group will receive six sessions of EA starting from 1 day before the surgery to the third day after the surgery. On the day of surgery, the EA session will be performed 30 min before the surgery until the surgery ends; while on all other days, the EA session will be performed in the afternoon. All acupuncture sessions will be delivered by experienced acupuncturists according to the standard operating procedures at the acupoints as follows: DU23 (Shangxing), DU20 (Baihui), DU29 (Yintang), LI4 (Hegu), PC6 (Neiguan), LU9 (Taiyuan), ST36 (Zusanli), ST37 (Shangjuxu), and LR3 (Taichong), all of which are selected based on the previous systematic review and our clinical experience (17). Disposable sterile stainless steel acupuncture needles (40 mm in length and 0.25 mm in diameter) will be inserted at the acupoints to a depth of 10–20 mm, which will be determined by the acupuncturists according to the participants’ body type. De qi sensation will be obtained through rotating the needles, and then the needles on the DU23 (Shangxing), DU29 (Yintang), PC6 (Neiguan), and LU9 (Taiyuan) acupoints will be stimulated using the HANS acupoint nerve stimulator (HANS-200A; Nanjing Jisheng Medical Co) at a constant frequency of 2 Hz and an intensity of 5 mA for 30 min per session. Participants assigned to the control group will receive the same course of treatment as the EA group. However, the acupuncturists will withdraw the needles immediately without De qi sensation, and the EA device will be connected to the acupoints by insulating tapes without the current passing.

### Outcome measurement

All the outcome measurements will be performed by an independent researcher who will be blinded to the group allocation.

### Primary outcome measures

The primary outcomes will measure changes in the STAI-S6 scores between the baseline and on the day of the surgery. The STAI-S6 will be used to assess the anxiety levels during the perioperative period. It is a standardized short form of the Spielberger STAI, in which the 40 questions of the Spielberger STAI have been reduced to three anxiety-present and three anxiety-absent questions (24, 25). Because of its simplicity, the STAI-S6 can be completed rapidly by participants, and it has been used to assess anxiety levels, including surgery-related anxiety levels, in many previous studies (16, 26).

### Secondary outcome measures

Besides the primary outcome measurement, the STAI-S6 will be assessed 1 day before the surgery, 1 day after the surgery, and 3 days after the surgery as well, aiming to observe the anxiety levels during the perioperative period. Assessment for the each group at other time points except the baseline will be conducted following 30 min of the intervention.

The stress response will be evaluated by measurement of the levels of plasma cortisol (Cort), adrenocorticotropic hormone (ACTH), interleukin-6 (IL-6), and tumor necrosis factor-α (TNF-α). The stress response to surgery is characterized by activation of the HPA axis and the SNS, in which ACTH synthesized by the anterior pituitary and Cort secreted by the adrenal cortex are the two representative hormones that increase in response to a surgical stimulus (7). It is well established that IL-6 and TNF-α participate in the activation of the HPA axis and increase plasma concentrations of ACTH and Cort (27). The levels of both of these cytokines have been measured in previous studies to evaluate the intensity of surgery-related stress response (28, 29). The levels of plasma Cort, ACTH, IL-6, and TNF-α will be measured 1 day before the surgery and 1 and 3 days after the surgery. To avoid the influence of circadian fluctuation, the plasma samples will be obtained strictly at the same time in the morning.

The Amsterdam Preoperative Anxiety and Information Scale (APAIS) will be used to specifically assess the preoperative anxiety levels. This scale consists of four questions related to anxiety and has been proven to correlate well with the full version of the STAI (30). The Chinese version of the APAIS has a high degree of reliability and validity for the Chinese population in the evaluation of preoperative anxiety (31). The APAIS will be assessed at the baseline, 1 day before the surgery, and on the day of the surgery.

To evaluate recovery, the first exhaust time after surgery and postoperative quality of recovery (QoR)-15 scores will be used. The first exhaust time has been frequently used in many clinical trials for assessing postoperative gastrointestinal function recovery (32, 33). The QoR-15 is a patient-reported outcome questionnaire that focuses on the quality of recovery after surgery and anesthesia (34). It has been widely used in surgery-related clinical trials as a measurement instrument for postoperative quality of recovery, and both the English and Chinese versions have been shown to have good content validity and internal consistency (35). The QoR-15 will be assessed 1 and 3 days after the surgery.

The postoperative pain will be evaluated using the numeric rating scale for pain, which is a single 11-point numeric scale with 0 representing “no pain” and 10 representing “worst pain imaginable” (36). All participants will be asked to report pain intensity in the last 24 h on the first, second, and third day after the surgery. Dosage of postoperative analgesics will also be recorded as an indicator of the pain condition.

### Adverse events and safety

Routine blood, renal function, and liver function tests will be conducted during the trial to ensure the safety of the participants. Adverse events including postoperative adverse reactions, such as infection, nausea, and vomiting, as well as potential adverse events related to acupuncture, such as palpitation, fainting, and bleeding, that occur from the time of signing the informed consent form till the last follow-up will be recorded. Regardless of a causal relationship with the study intervention, any adverse medical reaction that occurs will be evaluated and immediately reported to the primary investigator and ethics committee to decide if the patient needs to withdraw from the trial.

### Data collection and management

Screeners will collect the demographic and baseline characteristic data when the patients are recruited. Outcomes assessors will evaluate the clinical outcomes from 1 day before the surgery to 3 days after the surgery. The anxiety-related questionnaires will be completed by the subjects independently in the ward where outcome assessors will be available to answer questions. To maintain the participants’ confidentiality, only personal and study-related information will be collected and stored with restricted access. A data administrator will be responsible for cleaning, identifying, encoding, and converting the initial data to the appropriate format for data analysis. Subjects may withdraw from the study irrespective of the timing and reasons. The withdrawal data and reasons for withdrawal will be recorded. A data monitoring committee composed of independent researchers will monitor the study.

### Statistical analysis

The statistical analysis of all data will be performed by two analytical researchers, independent of the trial. All the outcomes will be subjected to an Intent-to-Treat analysis based on the initial allocation. For missing data, the multiple imputation method will be applied. IBM SPSS Statistics (version 25.0) will be used for statistical analysis. All continuous variables conforming to normal distribution will be expressed as mean ± standard deviation, while those that do not conform to normal distribution will be expressed as median and quartile spacing. For enumerative variables, frequency and the corresponding percentage will be provided. To compare variables between the two groups, independent samples *t*-test for normally distributed data and the nonparametric Mann–Whitney *U* test for non-normally distributed data will be used. Different time point assessments will be analyzed using generalized estimating equation. Differences within groups will be assessed using the paired *t*-test for normally distributed data and the Wilcoxon signed-rank test for non-normally distributed data.

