## Methods

### Study design

This study is a randomized, single-center, parallel, and controlled clinical trial in strict accordance with the Consolidated Standards of Reporting Trials (CONSORT) and Standards for Reporting Interventions in Clinical Trials of Acupuncture (STRICTA) guidelines (21–23). This study will be conducted to evaluate the effect of EA on perioperative anxiety and stress response in patients undergoing resection of gastric or colorectal cancer. The study will be conducted in Yueyang Hospital of Integrated Traditional Chinese and Western Medicine, affiliated to Shanghai University of Traditional Chinese Medicine. A total of 78 patients will be recruited and randomly divided 1:1 into an EA group and a control group. The study design is depicted in Figure 1 and the schedule of this trial is shown in Table 1.

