### Sample size

According to the difference in the six-item short form of the State-Trait Anxiety Inventory (STAI-S6) scores between the two groups at the baseline and on the day of the surgery, the required sample size of each group will be calculated by the data statistician. Based on our previous pilot study, the difference in the standard deviation of STAI-S6 scores is 4.04 points. The STAI-S6 score changes 6.11 points in the EA group and 2.78 points in the control group. On the basis of a 5% false-positive error rate (α = 0.05, two-sided) and 80% power (β = 0.2), the sample size is estimated as follows:

$$\text{n}=\frac{2\,{\left({\text{Z}}_{\alpha /2}+{\text{Z}}_{\beta }\right)}^{2}\times \sigma^{2}}{{\left(\mu_{2}-\mu_{1}\right)}^{2}}=\frac{2\,{\left(1.96+1.28\right)}^{2}\times 4.04^{2}}{{\left(6.11-2.78\right)}^{2}}\approx 31$$

A sample size of at least 31 participants should be recruited in each group. Assuming a dropout rate of approximately 20%, a total of 78 participants will be enrolled in the trial.

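### The comparison described for the primary STAI-S6 change conditions on neither baseline nor the stratification factors, and the test and effect measure are left to a normality check

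*Protocol article*

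**What the plan says.** The primary outcome is one change score per participant (Primary outcome measures): "The primary outcomes will measure changes in the STAI-S6 scores between the baseline and on the day of the surgery".

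Allocation is 1:1 and restricted (Randomization and blinding): "Randomization will be stratified by the surgery site (stomach or intestine) and age (<60 years or ≥60 years").

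The Statistical analysis section makes three statements that bear on the primary comparison:
- For variables compared between the groups: "independent samples *t*-test for normally distributed data and the nonparametric Mann–Whitney *U* test for non-normally distributed data will be used".
- For repeated assessments: "Different time point assessments will be analyzed using generalized estimating equation". No covariates are listed.
- For incomplete data: "For missing data, the multiple imputation method will be applied".

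Neither baseline STAI-S6, surgery site nor age appears as a covariate anywhere. The article does not say whether the two-sample test or the GEE carries the primary conclusion. The Sample size section rests on an unadjusted two-sample comparison of change, with "5% false-positive error rate (α = 0.05, two-sided) and 80% power (β = 0.2").

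**The concern.** Three features of the plan do not fit together well.

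1. **Baseline.** Subtracting baseline fixes its regression slope at 1. If the true slope is lower, the change score over-corrects chance imbalance in baseline and carries extra noise that a model conditioning on baseline would remove.
2. **Strata.** Stratified randomisation removes between-arm variation due to site and age. An unadjusted standard error still counts that variation. If the factors predict the change, the standard error is too large and the test is conservative.
3. **Choice of test.** One branch compares means and the other compares ranks, so the effect to be reported is unknown until the data have been seen. The Mann-Whitney branch also gives no mean difference with a standard error that standard Rubin's rules could pool, although multiple imputation is planned and dropout of about 20% is assumed.

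At stake are precision, a significance level that matches its nominal value, and a primary result whose form is fixed in advance.

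**Working it through.** **Inputs from the Sample size section.** Changes of 6.11 and 2.78 points, so a difference of 3.33; SD 4.04, taken here as the SD of the change; two-sided alpha 0.05; 31 per group; dropout about 20%.

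**Inputs not in the article, so assumed.** Correlation rho between baseline and day-of-surgery STAI-S6, 0.3 to 0.7; ratio of follow-up to baseline SD; share R² of the variance explained by the strata, 0.05 to 0.20.

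**Step 1: the plan's own figure.** n = 2(1.96 + 1.28)² × 4.04² / 3.33² = 30.9, so 31 per group. Then 31/0.8 = 38.75, so 39 per group and 78 in total. This reproduces. The 1.28 is the normal quantile for 90% power, not the stated 80%. That is a separate matter, but it explains why the power below exceeds 80%.

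**Step 2: the planned unadjusted test.** SE = 4.04 × √(2/31) = 1.026. Power from the noncentral t distribution with 60 degrees of freedom is 89.1% (90.1% by the normal approximation).

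**Step 3: conditioning on baseline.** Let s_B and s_F be the baseline and follow-up SDs, and b = rho × s_F / s_B the slope on baseline.
- Variance of the change: s_F² + s_B² − 2 rho s_F s_B
- Residual variance given baseline: s_F²(1 − rho²)
- Their difference: s_B²(1 − b)²

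The gain is therefore never negative at this level and vanishes only at b = 1. With s_F = s_B the ratio of the two variances is (1 + rho)/2:

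| rho | variance ratio | SD used | SE at 31 per group | power |
|---|---|---|---|---|
| planned test | 1 | 4.04 | 1.026 | 89.1% |
| 0.3 | 0.65 | 3.257 | 0.827 | 97.7% |
| 0.5 | 0.75 | 3.499 | 0.889 | 95.8% |
| 0.7 | 0.85 | 3.725 | 0.946 | 93.4% |

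The variance falls by 35%, 25% and 15%; the SE falls by about 19%, 13% and 8%.

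**Step 4: unequal variances.** Take s_F = 1.4 s_B, with s_B = 1. At rho 0.7, b = 0.98, the residual variance is 1.96 × 0.51 = 1.00 and the change variance is 1.96 + 1 − 1.96 = 1.00, so there is no gain. At rho 0.3, 1.784/2.12 = 0.84, a cut of 16% instead of 35%.

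**Step 5: strata left out.** If the arms are balanced within strata, the true variance of the difference is (1 − R²) times what the unadjusted test assumes. The actual two-sided level is then about 2Φ(−1.96/√(1 − R²)):
- R² 0.05: 1.96/0.975 = 2.01, level 4.4%
- R² 0.10: 1.96/0.949 = 2.07, level 3.9%
- R² 0.20: 1.96/0.894 = 2.19, level 2.8%

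Simulation of a balanced stratum gave about 4.5%, 4.0% and 3.0%, against about 5% with the stratum in the model. A second simulation used 62 patients, four strata, blocks of 4 and 3,000 runs per setting. With strata explaining 20% of the follow-up variance left after baseline, the unadjusted test ran at 3.4% to 3.8% and the adjusted model at 4.7% to 5.1%.

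**Step 6: switching by a normality check.** In the second simulation, with normal data, the switching rule had nearly the same type I error as the t-test alone (for example 3.5% against 3.4%, and 4.7% against 4.8%).

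**The case against.** The case for leaving the plan alone has real force.

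- **Baseline is used.** The change score subtracts it from every participant's value. A reader might infer that baseline is ignored and chance imbalance goes unhandled. The article does not support that: baseline enters, but less efficiently than it could.
- **Nothing is invalid or underpowered.** A reader might infer bias, an inflated false-positive rate or a power shortfall. None follows. Any error in the level is on the conservative side, and 89% is above the stated 80%. Nor was an error-rate cost of the normality check shown for normal data. What remains there is the undefined effect measure.
- **The primary analysis may be the GEE.** The sentence on t and U tests is general, and STAI-S6 is measured at five times. This stands as an uncertainty, so the two-sample test cannot be called the declared primary analysis. It does not rescue the plan, because the GEE names no covariates either, and a second candidate makes the choice less fixed.
- **The size is assumed.** The article gives no correlation, no separate variances and no stratum effect. Stable effects of age or site on anxiety level would partly cancel in a change score, so R² may be small. This stands. It limits confidence in the size of the gain.
- **The rank statistic can be pooled in principle.** U divided by the product of the group sizes estimates a probability and has a variance. That is correct. The difficulty is confined to the Mann-Whitney branch and to pooling a mean difference.
- **Covariate lists belong in a statistical analysis plan.** Often so, but this article goes further and prescribes specific unadjusted tests.

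**Conclusion.** The point holds as one of efficiency and prespecification. The only between-group test described for a single score is unadjusted and selected by the data, the strata used in randomisation are dropped from the analysis, and no method is named as primary.

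The planned test is valid and adequately powered, at about 89% with 31 per group. With equal variances and rho of 0.3 to 0.7, conditioning on baseline would cut the variance by 35% to 15% and raise power to about 98% to 93%. The gain shrinks as the follow-up variance grows and is nil when the baseline slope reaches 1. With stratum R² of 0.05 to 0.20, the nominal 5% test runs at about 4.5% to 3%.

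All these ranges rest on assumed values of rho, the variance ratio and R². That the primary test and effect measure are left open does not depend on them.

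**What to change.** Name one primary analysis: a linear model of day-of-surgery STAI-S6 on treatment, with baseline STAI-S6, surgery site and age stratum (below 60, or 60 and over) as covariates. Report the adjusted mean difference with its 95% confidence interval, pooled over the imputed data sets by Rubin's rules. Drop the normality check as the way to select the primary test, and keep the Mann-Whitney test as a sensitivity analysis. State that the GEE is supportive, and give it the same stratum terms and the baseline value.

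The cost is wording only. Baseline STAI-S6, site and age are already collected, no extra patients or visits are needed, and the named software fits the model. The Trial status section says that recruitment is still under way, so the choice could be recorded before the data are analysed.

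### GEE is named for the secondary repeated assessments with at most 39 patients per arm and no small-sample correction; with an uncorrected robust Wald chi-square test, joint group-by-time tests would run at about 6% to 8% instead of 5%

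*Protocol article*

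**What the plan says.** Three parts of the protocol article bear on this.

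- **Statistical analysis.** The only sentence on repeated measures is "Different time point assessments will be analyzed using generalized estimating equation". Two-group comparisons are covered separately: "To compare variables between the two groups, independent samples" t-tests are named for normally distributed data and the Mann-Whitney test otherwise. The analysis is by intention to treat with multiple imputation.
- **Outcomes.** The primary endpoint is one change score: "The primary outcomes will measure changes in the STAI-S6 scores between the baseline and on the day of the surgery". The other STAI-S6 assessments are secondary: "the STAI-S6 will be assessed 1 day before the surgery, 1 day after the surgery, and 3 days after the surgery as well". With baseline and the day of surgery, STAI-S6 has five times, as Table 1 also shows. Cortisol, ACTH, IL-6 and TNF-α each have three.
- **Sample size.** The calculation is made "On the basis of a 5% false-positive error rate" ("α = 0.05, two-sided"). It requires 31 per group, and 78 patients in total are enrolled after allowing for 20% dropout.

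The article does not state the working correlation, the covariance estimator, the coding of time, the hypothesis tested, the reference distribution or any small-sample correction.

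**The concern.** The usual GEE test uses the robust covariance and refers a Wald statistic to chi-square. Both steps rely on a large number of patients. With few patients the robust covariance is too small on average, and the chi-square reference ignores the uncertainty in estimating it. The effect is slight for one contrast but grows with the number of contrasts tested together, because a larger covariance matrix is estimated from the same patients.

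At stake are the secondary claims about the course of anxiety over the perioperative period and about the surgical stress response, which the Discussion names as the trial's second aim. If these are judged at a nominal 5%, the actual false-positive rate would be somewhat higher and the intervals slightly too narrow.

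**Working it through.** **1. The plan's own figure.** Inputs from the Sample size section: SD 4.04; changes of 6.11 and 2.78, so a difference of 3.33; multipliers 1.96 and 1.28.

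n = 2 × (1.96 + 1.28)² × 4.04² / 3.33² = 30.9, so 31 per group. Then 31 / 0.8 = 38.75, so 39 per group and 78 in total.

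The enrolment figure is reproduced. (1.28 is the multiplier for 90% power, whereas the text states 80%; that is a separate matter and does not change the numbers used here.) The relevant range is therefore 39 per arm nominally and about 31 per arm with observed data at the assumed dropout.

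**2. Degrees of freedom, with time as a factor.**
- STAI-S6, five times, baseline treated as an outcome: 4 df.
- STAI-S6, four later times, baseline as a covariate: 3 df.
- Each stress marker, three times, baseline treated as an outcome: 2 df.
- Any single contrast: 1 df.

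**3. Type I error of the uncorrected robust Wald test.** Assume complete data, equal arms of size n and a saturated group-by-time model. The robust covariance divides by n where the unbiased one divides by n − 1, so the Wald statistic is W = T² × n/(n − 1). Here T² is Hotelling's statistic on ν = 2n − 2 degrees of freedom. Hence, for p contrasts with c the 95% point of chi-square on p df:

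P(W > c) = P( F[p, ν − p + 1] > c × (n − 1)/n × (ν − p + 1)/(ν p) )

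Example with n = 39, p = 4: 9.488 × 38/39 × 73/(76 × 4) = 2.220, and P(F[4, 73] > 2.220) = 0.0751.

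| df | 31 per arm | 39 per arm |
|---|---|---|
| 1 | 5.9% | 5.7% |
| 2 | 6.6% | 6.2% |
| 3 | 7.4% | 6.8% |
| 4 | 8.3% | 7.5% |

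**4. Check by simulation, 4-df test.** With 20,000 runs per setting (exchangeable correlation 0.3 and 0.5, AR(1) 0.7, and one skewed setting at 31 per arm), the error was 8.0% to 8.5% at 31 per arm and 7.1% to 7.6% at 39. Actual GEE fits (exchangeable, 1,500 runs) gave 8.8% and 8.2%, with a Monte Carlo standard error of about 0.7 points.

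**5. Other specifications that the same sentence allows.**
- Model-based covariance, exchangeable assumed and true: 4.7% to 5.3% in the simulations, 5.4% to 5.7% in the GEE fits.
- Model-based covariance, exchangeable assumed but AR(1) true: about 7%.
- One contrast, or a linear time trend: 5.4% to 6.1%.
- Covariance with divisor n − 1 and an F reference, 4 df: 4.7% to 5.2%.

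**6. Interval width for one contrast.** Corrected over uncorrected is t × √(n/(n − 1)) / 1.96. At 31 per arm: 2.000 × √(31/30) / 1.96 = 1.04. At 39 per arm: 1.992 × √(39/38) / 1.96 = 1.03.

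**The case against.** The strongest reply is that the article does not commit to the test examined here. Its one sentence names GEE and leaves the joint hypothesis, time coding, covariance estimator and reference distribution open. Such details commonly sit in a statistical analysis plan, which is not shown, and a corrected GEE would be fully consistent with the sentence. This stands, and it makes every figure above conditional. A reader might infer that GEE at this sample size means an error rate near 8% for STAI-S6. The document does not support that: other permitted specifications give about 5% to 7%, and 8.3% belongs to 31 patients per arm, whereas intention to treat with multiple imputation makes the nominal number 39.

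A reader might also infer that the primary result is at risk. It is not, if the single change score is compared by t-test. Even if that contrast were read from an uncorrected robust GEE, its error would be 5.7% to 5.9%.

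Two further points stand. The 5% level appears only in the sample size calculation, so applying it to the secondary tests is an assumption. And GEE is an accepted method for repeated measures, so the choice in itself is not an error.

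What does not follow is that nothing need be said. A large-sample method is named for a small trial, and switching to a model-based covariance is safe only if the working correlation is right, which is not known in advance.

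**Conclusion.** The point holds in conditional form and is minor, since it touches secondary analyses only. If the repeated assessments are tested with an uncorrected robust Wald chi-square and time as a factor, the joint group-by-time error at 39 (31) per arm is about 7.5% (8.3%) for STAI-S6 at five times, 6.8% (7.4%) with baseline as a covariate, and 6.2% (6.6%) for each stress marker. The excess over 5% thus ranges from 1.2 to 3.3 points for joint tests, and is 0.7 to 0.9 points for a single contrast.

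These figures assume complete data, equal arms and a saturated model. The pooled test after multiple imputation was not evaluated. The 3-df figures also ignore the few degrees of freedom spent on covariates.

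**What to change.** For the repeated assessments, state one of the following:

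- a linear mixed model for repeated measures with unstructured covariance, the baseline value and the two stratification factors (surgery site and age group) as covariates, and Satterthwaite or Kenward-Roger degrees of freedom; or
- GEE with the same covariates, a small-sample corrected covariance (Mancl-DeRouen or Kauermann-Carroll) and a t or F reference.

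For outcomes without a baseline measurement, such as QoR-15, the baseline term drops out.

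The change is to analysis wording only and needs no further patients or measurements. The article reports that recruitment is still under way, so it could be made before the results are known. The cost is single-contrast intervals about 3% (39 per arm) to 4% (31 per arm) wider. Markedly skewed markers may need transforming before a mixed model is used.
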